#### Outcomes to be included within the full study

The following outcomes listed below will be included in the pilot study since participants in the pilot may be rolled into the full study (see Table 1). The primary outcome in the full study will be the SPADI and secondary outcomes will include:• *General health status* as measured by EQ-5D global health^
13
^ and Single Assessment Numeric Evaluation^
14
^• *Shoulder specific function tests*: American Shoulder and Elbow Surgeon’s Score,^
15
^ Shoulder Pain and Disability Index,^
16
^ Simple Shoulder Test^
17
^• *Patient satisfaction*: Surgical Satisfaction Questionnaire (SSQ-8)• *Patient Anxiety *as measured by the Decisional Regret Scale,^
18
^ and Patient Anxiety Symptom Scale (PASS)• *Adherence to rehabilitation* as recorded in the patient log (see Table 1)• *Performance measures*: goniometric measures of shoulder range of motion

**Table 1. table1-17589983251345393:** DRS, decisional regret scale; SPADI, shoulder pain and disability index; SANE, Single assessment of the numeric evaluation; PPQ, patient participation questionnaire; SSQ-8, surgical satisfaction questionnaire; SAQ, surgical anxiety questionnaire.

Variable/outcome	Hypothesis	Outcome measure	Method of analysis
Recruitment	15-16/ month And 50% eligible to participate	Research log	Percentages reported

Adherence	80% of all participants in the intervention groups complete the PREPS program, and 60% report exercise at least 3 times per week	Patient log	Percentages reported
Content acceptability	60% of participants found the treatment useful and helpful on item 7	Surguical satisfaction quesionnaire	Means and standard deviation reported
Study acceptability	60% of participants found the treatment delivery acceptable, and reported being likely to use this treatment again and recommend it to others, on item 10	Surguical satisfaction quesionnaire	Means and standard deviation reported
Treatment fidelity	If 80% of phone calls and recorded notes were documented on the checklist by the therapist	Therapist checklist	Means and standard deviation reported

The majority of assessments will occur at baseline, day before surgery, and post-surgery at 6 weeks, 3 months, 6 months and 12 months. With the exception of some measures, as detailed in Figure 1, of the schedule throughout the research study.

#### Data management and monitoring

Data collection and management procedures have been approved by the Western University Research Ethics board (#120163) and Lawson Health Research Board (R-23-550). Identifiable data will be kept separate from the main data files and will be accessible to authorized study team members only. Data entry and coding of the de-identified data will be conducted by a blinded research assistant. If any adverse events occur that are study related, they will be discussed by the research team collectively. 

## Sample size estimation

Our sample size calculation will be based on a formula for analysis of covariance (ANCOVA), with an estimated association between preoperative and postoperative SPADI scores at 3 months.^
19
^ Correlation of SPADI scores from baseline and 3 months will be determined from pilot trial findings, however, we have estimated a calculation based on current literature of the SPADI in arthroplasty patients.^19,20^

Calculation: N per group = 2((Z_α_ + Z_β_)^2^σ^2^(1-r^2^))/(δ-M)^2^, where:

α = the probability of making a Type I error = 0.05, one-sided test

1-β = the power to detect a difference if one truly exists = 0.80, thus, β = 0.20

δ = MCID (within-group) = 20.6, adjust for between-groups comparisons 20.6*0.5 = 10.3

r = at 3 months = 0.81

σ = 21.3 (SD at 1 year post-operative)^
20
^

M = 0.2 SD (4.26), margin for non-inferiority (Group 1 v Group (2) and superiority (Group 1 v SOC)

N per group = 2((1.64 + 0.84)^2^ (21.3)^2^(1-0.81^2^))/(10.3-4.26)^2^ = 53 patients per group

The estimate per group will then be increased by 5% to adjust for potential losses over time (*n* = 56/group).

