### Participants

We will recruit volunteers over the age of 18 years, who have been consented for a shoulder replacement surgery at the HULC, to fulfill a sample size of 90 participants, with 30 in each arm. The sample size is based on current recommendations for pilot studies, objectives of this study, and feasibility of being able to complete recruitement of the full powered trial in 2 years. Since our sample size is 168 in the full powered trial, we aim to collect half of this in 1 year. See below for full trial sample calculation.

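### The full-trial sample size applies one superiority-by-margin formula to the non-inferiority comparison as well, so the stated 80% power is unsupported there (about 54% if Groups 1 and 2 are truly equal)

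*Protocol article*

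**What the plan says.** The Sample size estimation section of the protocol article plans the full trial on an ANCOVA of SPADI at 3 months. The formula is "N per group = 2((Z_α_ + Z_β_)^2^σ^2^(1-r^2^))/(δ-M)^2". The inputs are:

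- Type I error: "α = the probability of making a Type I error = 0.05, one-sided test"
- Power: "1-β = the power to detect a difference if one truly exists = 0.80, thus, β = 0.20"
- Effect: "δ = MCID (within-group) = 20.6, adjust for between-groups comparisons 20.6*0.5 = 10.3"
- Correlation: "r = at 3 months = 0.81"
- Standard deviation: "σ = 21.3 (SD at 1 year post-operative"), a 1-year value
- Margin: "M = 0.2 SD (4.26), margin for non-inferiority (Group 1 v Group (2) and superiority (Group 1 v SOC")

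The result is 53 per group, raised by 5% to 56, which in three arms is 168. The section gives no second calculation and no assumed true difference between Group 1 (self-directed programme) and Group 2 (the same programme with therapist calls). It says that r will be determined from the pilot and does not say the same of σ.

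**The concern.** The two tests place the null boundary on opposite sides of zero. Let D be the true benefit of Group 1 over its comparator.

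- **Superiority by a margin (Group 1 v standard of care).** The null is D ≤ +M. With true benefit δ, the distance from the boundary is δ − M.
- **Non-inferiority (Group 1 v Group 2).** The null is D ≤ −M. The distance from the boundary is D + M, which is M alone if the arms are equal.

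The sign of M has to change between the tests. The article uses δ − M for both, so the power it reports belongs to the first test only. If the full trial were run on this basis, an inconclusive non-inferiority result could be close to a coin toss even if the therapist calls add nothing. A reader would wrongly believe that the comparison had 80% power.

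A second, smaller mismatch sits in the same calculation: σ is a 1-year value, whereas r and the analysis time point are at 3 months.

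**Working it through.** **Inputs (all from Sample size estimation).** σ = 21.3, so σ² = 453.69. r = 0.81, so 1 − r² = 0.3439. Adjusted variance = 453.69 × 0.3439 = 156.02 (adjusted SD 12.49). One-sided α = 0.05, power 0.80, δ = 10.3, M = 4.26. The only input not in the article is the true difference between Groups 1 and 2, which is varied below.

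**1. Reproduce the stated figure.**
Numerator = 2 × (1.64 + 0.84)² × 156.02 = 1919.2.
Denominator = (10.3 − 4.26)² = 6.04² = 36.48.
N = 1919.2 / 36.48 = 52.6, so 53 per group. Then 53 × 1.05 = 55.7, so 56, and 3 × 56 = 168. All three figures agree with the article.

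**2. Power for Group 1 v standard of care at 53.**
SE = √(2 × 156.02 / 53) = 2.43.
Power = Φ(6.04 / 2.43 − 1.645) = 80%. The stated power is right for this test.

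**3. Power for non-inferiority at 53.**
Power = Φ((4.26 + D) / 2.43 − 1.645), with D positive when Group 1 is better.

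| True D | Distance to null | Power |
|---|---|---|
| 0 | 4.26 | 54% |
| −1 | 3.26 | 38% |
| −2 | 2.26 | 24% |
| +1.78 | 6.04 | 80% |

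At equality, a t-based calculation also gives 54%. If all 56 per group are evaluable, power is 56%.

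**4. Size needed for 80% at equality.**
With the article's rounded Z values, 1919.2 / 4.26² = 105.8, so 106 per group. With unrounded Z values it is 107. Adding 5% gives 107 × 1.05 = 112.4, so 113 per group, or 339 in three arms.

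**5. Does the article's own δ rescue the formula?** No. If Group 1 were truly 10.3 points better than Group 2, the distance would be 10.3 + 4.26 = 14.56 and N = 1919.2 / 14.56² = 9.1, so 10 per group. The formula therefore does not fit this test at the article's δ either. Equality only sets the size of the shortfall.

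**6. Dependence on r and σ.** With σ and M unchanged, non-inferiority power at equality with 53 per group is 42% at r = 0.7 and 32% at r = 0.5. Because M is defined as 0.2σ, σ cancels from the non-inferiority size at equality: N = 2 × 2.48² × 0.3439 / 0.2² = 105.8 whatever σ is. A different 3-month σ would instead change the Group 1 v standard of care calculation, through both σ² and δ − M. The article gives no 3-month SD, so neither the direction nor the size of that change can be stated.

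**The case against.** The strongest reply is that this calculation does not size the study being run. That study is a 90-patient pilot with feasibility questions, and its Plan for statistical analyses is descriptive with progression criteria. The section is also openly provisional, and the full trial can be re-sized before it starts. This stands, and it limits how serious the point is. It does not remove it: the article says that pilot participants may be carried into the full study, and putting a new r into the same formula would repeat the error.

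A second reply is that equality is the reviewer's assumption. That also stands. The 54% is conditional, and a reader who infers that power simply is 54%, or that the sponsor assumed equality, goes beyond the text. What can be said without any assumption is that nothing stated supports 80% for this comparison.

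Two further readings are tempting and are not supported:

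- **That the error carries through to the pilot's size**, because of "Since our sample size is 168 in the full powered trial, we aim to collect half of this in 1 year". The Participants section also cites pilot-study recommendations and the study objectives, and Trial design adds the sex/gender analysis. Half of 168 is 84, not 90, and the monthly recruitment target is nowhere derived from 168.
- **That the 1-year σ makes the trial too small.** The article gives no 3-month SD to compare it with.

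**Conclusion.** The point holds for the planned full trial. The arithmetic is correct; the fault is using one formula for two hypotheses. The 53 (56) per group supports 80% power only for Group 1 v standard of care. For non-inferiority with M = 4.26 it gives about 54% if the arms are equal and 53 per group are evaluable (56% with all 56). Power is lower if Group 2 is truly better, and reaches 80% only if Group 1 is truly about 1.8 points better, which the article neither states nor argues. These figures rest on the article's σ, r and one-sided 0.05. The sample size section should be corrected before the full trial is fixed; the pilot's feasibility endpoints and progression decisions do not depend on it.

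**What to change.** In Sample size estimation:

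1. State that 53 (56) per group gives 80% power only for superiority of Group 1 over standard of care beyond M, at a true benefit of 10.3.
2. For Group 1 v Group 2, either state the assumed true difference and report the power that follows (about 54% at no true difference, from the same numerator over M²), or make it an estimation comparison reported with its confidence interval.
3. When r is re-estimated from the pilot, also estimate σ at 3 months from the pooled pilot data, recompute M as 0.2 of that SD, and rerun both calculations.

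The cost is rewording and a less favourable power figure for one comparison. No extra patients are needed unless the sponsor wants 80% non-inferiority power at equality, which on present inputs would take about 107 evaluable per group (113 after the 5% allowance).

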## Plan for statistical analyses

Descriptive quantitative variables will be presented as means and standard deviations and the categorical variables will be presented as percentages. Following pilot study guidelines, criteria to progress from feasibility to definitive trial are listed in Table 2 below. Each primary feasibility outcome measure will be assessed separately, and overall progression will be determined by the worst-performing criterion. If all signals fall into the green zone, we will proceed to the trial without changes. If none of the signals fall into the red zone but at least one falls into the amber zone, the design of the trial procedures will be amended before proceeding to the definitive trial. If at least one signal falls into the red zone, we will not proceed to the definitive trial without making significant improvements to protocol and re-assessing feasibility.

**Table 2. table2-17589983251345393:** Progression criteria for feasibility.

	Proceed	Proceed with protocol amendment	Significant protocol amendment
Recruitment *N* = 90 in 12 months	15-16/ month and 50% eligible to participate	13-14/ month and 40% eligible to participate	<12 /month and 30% eligible to participate
Adherence	• 80% of all participants in the intervention groups complete the online program, and 60% report exercise at least 3 times per week	• 60% of all participants in the intervention groups complete the online program, and 40% report exercise at least 3 times per week	• 25% of all participants in the intervention groups complete the online program, and 25% report exercise at least 3 times per week
Content acceptability	• 60% of participants found the treatment useful and helpful with a score of 7/10	• 40% of participants found the treatment useful and helpful with a score of 7/10	• <40% of participants found the treatment useful and helpful with a score of 7/10
Study acceptability	• 60% of participants found the treatment delivery acceptable, and reported being likely to use this treatment again and recommend it to others with a VAS score of 7/10	• 40% of participants found the treatment delivery acceptable, and reported being likely to use this treatment again and recommend it to others with a VAS score of 7/10	• <40% of participants found the treatment delivery acceptable, and reported being likely to use this treatment again and recommend it to others with a VAS score of 7/10
Fidelity of treatment	• If 80% of phone calls and recorded notes were documented on the checklist by the therapist	• If 60% of phone calls and recorded notes were documented on the checklist by the therapist	If <40% of phone calls and recorded notes were documented on the checklist by the therapist

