#### Feasbility outcomes

• Recruitment Rate: We will proceed with the larger trial if we are able to recruit 90 participants within 24 months, and if at least 50% of eligible participants consent to participate.• Adherence: Adherence to the education program will be considered adequate if 80% of all participants in the intervention groups complete the full online program and report it on the log. Exercise programs will be considered adequate if 60% of participants in the intervention groups report exercise at least 3 times per week.• Content Acceptability: Content acceptability will be assessed using item 7 on the Surgurical Satisfaction Questionnaire, where acceptability will be considered adequate if 60% of participants were satistifed with the treatment (score of atleast 4/5 on item 7).• Study Acceptability: Study acceptability will be assessed using item 10 on the Surgurical Satisfaction Questionnaire, where acceptability will be considered adequate if 60% of participants were satistifed with the study (score of atleast 4/5 on item 10).• Treatment Fidelity: If 80% of the content was covered in 80% of phone calls fidelity checklist assessment, fidelity will be considered acceptable.

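### The recruitment progression criterion is internally inconsistent: Table 2's target of 90 in 12 months does not match its monthly bands if these count enrolled patients, and the feasibility text uses 24 months

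*Protocol article*

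**What the plan says.** Recruitment is named in the Introduction as a primary feasibility outcome. Its criterion appears in four places in the protocol article.

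- **Plan for statistical analyses, Table 2.** The row label sets the target at "90 in 12 months". Green is "15-16/ month and 50% eligible to participate", amber is "13-14/ month and 40% eligible to participate" and red is "<12 /month and 30% eligible to participate".
- **Table 1.** The recruitment hypothesis repeats the green cell: "15-16/ month And 50% eligible to participate".
- **Feasibility outcomes.** "We will proceed with the larger trial if we are able to recruit 90 participants within 24 months", provided that at least half of eligible patients consent.
- **Participants.** The pilot is "to fulfill a sample size of 90 participants, with 30 in each arm". The size is justified partly by "feasibility of being able to complete recruitement of the full powered trial in 2 years", and the stated aim is to collect half of the 168 full-trial patients in one year.

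The analysis section assesses each criterion separately and lets the worst one decide. A single red signal means that the definitive trial does not go ahead without significant improvement and a fresh feasibility assessment.

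**The concern.** A progression criterion should give one answer for one set of data. Here the target in the row label, the monthly bands beside it, the period in the feasibility text and the pace in the Participants section do not agree. The bands look about twice as high as the row's own target needs, and the text accepts half the pace of that target.

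What is at stake is the decision the pilot exists to inform. If recruitment meets one statement and falls below the red rate of another, the team would have to choose which statement governs after seeing the result. With the worst criterion decisive, that choice alone could settle whether the definitive trial proceeds.

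**Working it through.** **Inputs.** Pilot size 90 and full-trial size 168 (Participants); 12 months and the bands 15-16, 13-14 and <12 per month (Table 2); 24 months and at least 50% consent (feasibility outcomes); half of 168 in one year (Participants).

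**Step 1: can the stated green rate be reproduced?** Rate = patients / months.

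| Source | Calculation | Per month |
|---|---|---|
| Table 2 row label | 90 / 12 | 7.5 |
| Feasibility outcomes | 90 / 24 | 3.75 |
| Participants, one-year aim | (168 / 2) / 12 = 84 / 12 | 7.0 |
| Participants, full trial in 2 years | 168 / 24 | 7.0 |
| Full trial in 1 year (variant tried) | 168 / 12 | 14.0 |

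None gives 15-16. Working backwards, 15 × 12 = 180 and 16 × 12 = 192 patients a year. Equivalently, 90 / 15 = 6.0 and 90 / 16 = 5.6 months, a period that appears nowhere in the document. The 168 is not the source of the problem: the article's formula gives 52.6, hence 53 per group; 53 × 1.05 = 55.65, hence 56; and 3 × 56 = 168, as stated.

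**Step 2: the count read as enrolled patients.** The row's own target, 7.5, is half the lower green bound (7.5 / 15 = 0.5) and below the red rate of 12 (12 × 12 = 144 a year). The paces of 7.0 and 3.75 are below it too.

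**Step 3: the count read as eligible patients approached.** At 50% consent, 15 × 0.50 = 7.5 and 16 × 0.50 = 8 enrolled per month, or 90-96 in 12 months. This matches the row label.

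**Step 4: the feasibility text against Table 2 on both readings.** The slowest result the text accepts is 3.75 enrolled per month.

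- Enrolled reading: 3.75 is below 12.
- Approached reading: with at least 50% consent, at most 3.75 / 0.50 = 7.5 eligible patients per month were approached, again below 12. Approaching 12 a month and enrolling 3.75 would mean 3.75 / 12 = 31% consent, which fails the text's own 50% condition.

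So the conflict between the feasibility text and Table 2 does not depend on what the monthly count means.

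**Step 5: coverage of the bands.** Exactly 12 per month, and averages between 12 and 13 or between 14 and 15, belong to no zone. Each cell joins a rate and a percentage, and nothing says which zone applies when the two point to different ones.

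**The case against.** The strongest defence is that Table 2 never says its monthly figure counts enrolled patients. Read as patients approached, the green cell reproduces 90 in 12 months at 50% consent (Step 3) and sits close to the Participants pace of 7 per month. This stands as a possible explanation. It means that the defect inside Table 2 may be an unlabelled count rather than wrong numbers. It does not remove the conflict with the 24-month rule (Step 4).

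Four stronger readings are tempting, and the document does not support them.

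- *That recruiting 90 in 12 months is simply classed red.* This assumes that the count is enrolled patients, and it overlooks that the red cell also names 30%. A rate of 7.5 per month with 50% consent is then red on the rate and cannot be green, but it matches no cell in full.
- *That the 24-month rule commits the full trial to far more than two years.* 168 / 3.75 = 44.8 months ignores the statement, in the section on outcomes for the full study, that pilot participants may be rolled into it. If all 90 are, 168 − 90 = 78 remain, and 78 / 3.75 = 20.8 months after the pilot. Whether the two years include the pilot is not stated.
- *That the tables switch to an eligibility rate.* The table wording can be read that way, but it is more naturally shorthand for the consent share that the feasibility text defines. It needs tidying and is not a separate contradiction.
- *That the right bands follow from halving Table 2.* If the table's own percentages are applied, amber becomes 13 × 0.40 = 5.2 to 14 × 0.40 = 5.6 and red becomes below 12 × 0.30 = 3.6. These are not half of the printed rates, so the document does not determine the lower cut-points.

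**Conclusion.** The inconsistency is real and should be corrected before the criterion is applied. Two parts need no assumption about the monthly count: the target period is 12 months in Table 2 and 24 in the feasibility text, and the slowest result the text accepts falls below Table 2's red rate. The third part, that the row's own target of 7.5 per month misses green by a factor of two and lies below the red rate, holds only if the count is enrolled patients, which the article leaves open.

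The size is material: the paces derived from stated targets are 3.75, 7 and 7.5 per month, against a green band of 15-16. A pilot recruiting 3.75 per month with 50% consent may proceed under the text. Under Table 2 its rate is in the red range on either reading, so progression would be blocked if the worse component governs the row. That last condition is an assumption, because the worst-criterion rule is stated between criteria and not within one.

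The article format is no excuse, since the figures are printed and incompatible rather than omitted.

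**What to change.** 1. Choose one recruitment period and one rate, stated as **enrolled patients per month**, and use them in Participants, the feasibility outcomes, Table 1 and Table 2. Twelve months is better supported than 24: Table 2's label and the one-year aim in Participants agree to within 7.5 − 7.0 = 0.5 per month.
2. Set green at the rate the target requires: at least 7.5 per month for 90 in 12 months, or about 7 per month if the Participants pace is what is meant.
3. Rescale amber and red below that threshold so that the bands are contiguous. The sponsor should choose the cut-points, and record them before the data are seen.
4. Define the percentage everywhere as consented divided by eligible, as the feasibility outcomes section does.
5. State how rate and percentage combine when they fall in different zones, for example by taking the worse of the two.

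The cost is a revision of the feasibility outcomes criterion, one Table 1 cell and three Table 2 cells, plus an alignment of the Participants sentence if its pace is not the one kept. New cut-points are a decision for the sponsor and not mere wording, but nothing operational changes.

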We have developed a comprehensive, patient-centered program that combines exercise, preparedness for surgery, motivational interviewing, and pain management principles.^10,11^ The program is titled Pre-Rehab and Education Program before Surgery (PREPS). The intervention was developed in collaboration with patient partners on the wait list for a shoulder replacement, a transdisciplinary healthcare team (i.e., surgeons, physiotherapists, occupational therapists, and rehabilitation researchers), and current scientific literature. This patient-centered prehabilitation program has the potential to improve postoperative pain, function, and patient-oriented outcomes, and decrease postoperative opioid use and long-term healthcare costs.

Prior to testing the effectiveness of the intervention in a fully powered randomized controlled trial (RCT) we aim to complete a pilot randomized controlled trial to test the feasibility of the intervention and study protocol. Primary feasibility outcomes will be recruitment and retention of patients, given the challenges when sampling an older adult population. Additionally, we anticipate some technological challenges given the intervention will primarily be delivered virtually.

The study will aim to answer the following research questions:1. What is the acceptability and satisfaction with the PREPS program for patients undergoing a total shoulder replacement?2. How feasible is the PREPS program in terms of recruitment rate, adherence rate, retention rate, and participant burden?3. What outcome measures tested in the feasibility trial should be included within the full RCT?

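### The study-acceptability row that decides progression (Table 2) is worded about the treatment, whereas the outcome definition is satisfaction with the study

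*Protocol article*

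**What the plan says.** The protocol article describes study acceptability in three places.

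- **Feasibility outcomes (text).** The instrument is fixed: "Study acceptability will be assessed using item 10 on the Surgurical Satisfaction Questionnaire". The target is "60% of participants were satistifed with the study (score of atleast 4/5 on item 10"). Content acceptability is a separate outcome with its own item: "60% of participants were satistifed with the treatment (score of atleast 4/5 on item 7").
- **Table 1 (Outcomes to be included within the full study).** The study-acceptability row concerns treatment delivery, using the treatment again and recommending it. It still attributes these to the same item: "recommend it to others, on item 10".
- **Table 2 (Plan for statistical analyses).** The green cell, which sets a VAS cut-off of 7/10, reads "60% of participants found the treatment delivery acceptable, and reported being likely to use this treatment again and recommend it to others". Amber uses the same words at 40% and red at below 40%. Neither item 10 nor satisfaction with the study is mentioned.

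Table 2 holds the progression criteria, and the worst row decides. All green means proceeding unchanged. One red means not proceeding without significant improvements and a new feasibility assessment. The Introduction states the purpose of the pilot as "to test the feasibility of the intervention and study protocol".

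**The concern.** The text separates two questions: whether participants were satisfied with the treatment, and whether they were satisfied with the study. In Table 2 the second has been reworded as another question about the treatment, under an unchanged row name. The decision rule works from Table 2, so the rewording can change what the decision rests on.

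Participants may like PREPS and still find the trial itself burdensome: two pre-operative and four post-operative visits, questionnaires, and activity logs. A row about the treatment does not register that. The definitive trial could then be launched unchanged with procedures that participants had judged unacceptable. The study-acceptability row was the one place in Table 2 where participants would have rated the trial after entering it.

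**Working it through.** The 60% and 40% limits are set, not calculated, so there is no derived figure to reproduce. The check is a comparison of the three statements, followed by simple counts.

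**1. Side by side**

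| | Feasibility outcomes | Table 1 | Table 2 |
|---|---|---|---|
| Subject | the study | the treatment (delivery, reuse, recommendation) | the treatment (same three) |
| Source | item 10 | item 10 | a VAS; no item named |
| Cut-off | at least 4/5 | not given | 7/10 |
| Green | 60% | 60% | 60% |

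Table 1 departs from the definition in wording only. Table 2 departs in subject, source and cut-off.

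**2. Do other Table 2 rows cover the gap?** The other rows are recruitment, adherence, content acceptability and fidelity.
- Adherence and content acceptability concern PREPS.
- Fidelity concerns the therapist's calls and checklist.
- Recruitment includes the share of eligible patients who consent. This reflects willingness to enter the trial, not experience of it.

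So after consent, no row records how participants view the procedures.

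**3. Can the row be green when the defined outcome is not?** Inputs: 90 participants, 30 per arm (Participants section). If all 90 are counted, green needs 0.60 × 90 = 54, and red is fewer than 0.40 × 90 = 36. Suppose, for illustration only, that 72 endorse the treatment wording and 31 are satisfied with the study.
- Table 2 as written: 72/90 = 80%, green.
- The defined outcome on the same zones: 31/90 = 34%, red.

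The two can diverge in this way only if they come from different answers. Table 2's VAS makes that possible. A single item 10 response would give only one percentage.

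**4. Who can answer?** The comparator arm does not receive PREPS (Comparator section), so using this treatment again has no clear meaning for 30/90 = one third of participants. Table 2 says only that it counts participants. If Groups 1 and 2 form the denominator, green needs 0.60 × 60 = 36. If all 90 do, it needs 54. The document does not say which applies, or what the control arm would be rating.

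**5. How are three statements scored?** Table 2 gives one VAS score for delivery, reuse and recommendation. It does not say whether this is one overall rating or three ratings that must all reach 7/10. The scoring is ambiguous.

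**The case against.** **The wording may simply describe item 10.** Table 1 attaches the three-part phrase to item 10, so the tables may be paraphrasing one question. If item 10 supplies the number everywhere, one answer gives one percentage and the divergence in step 3 cannot arise. This stands as a limit: the problem depends on Table 2 being scored as written, and the text of item 10 is not shown. It does not remove the conflict. The definition says item 10 measures satisfaction with the study, Table 1 says it measures views of the treatment, and Table 2 names a different scale.

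**The trial is not wholly ungraded.** Consent is partly a response to randomisation, the visits and the one-year follow-up. This also stands. The gap is in participants' view of the procedures after consent.

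**A stronger reading does not stand.** A reader might infer that the joined wording would push a well-liked treatment into amber. If 80% endorsed each statement independently, 0.8³ = 51% would endorse all three, and the chance of at least 54 of 90 doing so is about 0.06. But the document nowhere says that three answers are collected and all three required. It also gives no ground for independence between three opinions about the same treatment, and the result depends heavily on that assumption. With 60 respondents the chance of green (at least 36) is about 0.11. Under an equicorrelated latent-normal model (an assumption) with correlations 0.3, 0.5 and 0.7, the joint share is 0.57, 0.61 and 0.66, and the chance of green with 90 respondents is 0.32, 0.63 and 0.90. The supportable statement is that the scoring is ambiguous.

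**Conclusion.** The contradiction is real and lies inside the progression rule. The definition concerns satisfaction with the study. The Table 2 row of the same name concerns the treatment, on another scale with another cut-off. If Table 2 is scored as written, a green grade in that row says nothing about whether participants accepted the study, and it is compatible with study satisfaction in the red range. Only the consent rate then bears on participants' acceptance of the trial procedures.

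This conclusion comes from the text and needs no calculation. The 80%/34% example shows that the two can diverge and is not a forecast. How far the grade would move cannot be determined, because the document does not give the wording of item 10, the respondents or the scoring of the three statements. It would be too strong to say that the problem holds whichever item is used: if item 10 asks about the study and supplies the Table 2 figure, only the wording of the tables is wrong. The point should be corrected before the progression criteria are applied.

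**What to change.** In Tables 1 and 2, replace the study-acceptability wording with the definition already under Feasibility outcomes: the share of participants in all three arms scoring at least 4/5 on item 10 for satisfaction with the study. Keep the zones at 60%, 40% and below 40%, remove the VAS reference from that row, and confirm that item 10 does ask about the study. If it does, no new question is needed.

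If treatment delivery, reuse and recommendation are to be kept, report them as separate percentages under treatment acceptability in Groups 1 and 2, outside the study-acceptability signal.

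The cost is rewording one row in two tables and checking one item on an existing form. The drawback is that the study signal may be less favourable than the treatment signal, which makes a green grade harder to reach.
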